#### Mechanism outcomes

2.4.3

Blood and fecal samples will be collected from all participants at baseline and at the end of the treatment period (week 4). Fasting blood samples (20 mL) will be drawn from the antecubital vein between 7:00 and 9:00 AM. The samples will then be centrifuged at 3,000 rpm for 15 min at 4°C, and the resulting serum will be stored at −80°C. Fecal samples will be collected immediately after morning defecation, placed into sterilized fecal containers, and stored at −80°C. The mechanisms of LSM will be examined through serum biochemical markers, gut microbiota composition, and metabolomic profiling.

Serum biochemical markers will include neurotransmitters, inflammatory cytokines, and endocrine hormones. Neurotransmitters to be measured are 5-hydroxytryptamine (5-HT) and gamma-aminobutyric acid (GABA). Inflammatory markers will cover interleukin-1β (IL-1β), interleukin-6 (IL-6), and tumor necrosis factor-α (TNF-α). Hormonal analysis will focus on melatonin and hormones associated with the hypothalamic-pituitary-adrenal (HPA) axis, such as adrenocorticotropic hormone (ACTH), corticotropin-releasing hormone (CRH), and cortisol (CORT). All measurements will be conducted using enzyme-linked immunosorbent assays (ELISA).

Gut microbiota composition in fecal samples will be analyzed through 16S rRNA gene sequencing. α diversity will be assessed using observed ASV, Shannon, Simpson, and Chao1 indices, while β diversity will be evaluated through principal coordinates analysis (PCoA) based on the Bray–Curtis distance matrix. The linear discriminant analysis effect size (LEfSe) model will be applied to identify differentially abundant taxa between groups.

Metabolomic profiling of serum samples will be performed using non-targeted liquid chromatography-mass spectrometry (LC-MS) (26). Principal component analysis (PCA) and partial least squares discriminant analysis (PLS-DA) will be used to visualize metabolic patterns across groups. Key differential metabolites will be identified based on variable importance in projection (VIP) scores from the PLS-DA model. Additionally, non-targeted quantification of short-chain fatty acids (SCFAs) in fecal samples will be conducted via gas chromatography-mass spectrometry (GC-MS) (27).

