### Sample size

2.8

To obtain a preliminary estimate of LSM’s efficacy, a pilot study was conducted with 12 participants assigned to each of the two groups, based on the rules of thumb (29). After the 4-week treatment period, ISI scores decreased by 6.82 ± 4.06 points in the LSM group and 3.24 ± 2.38 points in the WC group from baseline. The observed effect size (Cohen’s *d*) was 1.08, which, according to Cohen’s criteria (*d* = 0.2 as small, *d* = 0.5 as medium, and *d* = 0.8 as large), indicates a large effect. Based on these results, the sample size was calculated using the “Two-sample *t*-tests allowing unequal variance” module in PASS software, version 15.0, with a two-tailed alpha of 0.05 and a power of 0.90, while accounting for a 10% expected dropout rate. Previous studies have shown that endocrine therapy is an important risk factor for insomnia in breast cancer patients (9). Therefore, to account for potential heterogeneity in treatment response, the sample size was stratified by endocrine therapy status (yes vs. no). To ensure sufficient statistical power within both strata, the sample size was adjusted to 46 participants per group. Ultimately, considering the importance of using whole numbers for clear communication of results, and to further enhance the statistical power of the study, the sample size per group was rounded up to 50 participants.

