### Statistical analysis

2.9

The analysis will be conducted based on the intent-to-treat (ITT) population, defined as participants who complete baseline assessments and have at least one follow-up measurement. The Shapiro–Wilk test will be employed to assess the normality of the data distribution. For continuously measured repeated data, such as ISI scores, PSQI scores, PFS scores, FACT-B scores, and hypnotic medication dosages, a mixed-effects model adjusted for baseline values will be used to compare longitudinal changes from baseline across follow-up time points between groups. The model will include fixed effects for endocrine therapy status (yes or no), time, group, and the interaction between time and group, while treating individual participants as random effects. Given that mixed-effects models can accommodate participants with at least one outcome measurement, no imputation will be performed for missing values in the primary analysis (30).

For non-repeated continuous variables, such as serum biochemical markers and gut microbiota abundance, between-group comparisons will be performed using either the *t*-test or Mann–Whitney *U* test, depending on data distribution. Categorical variables, including treatment response rates and incidence of adverse events, will be analyzed using chi-square or Fisher’s exact tests. Correlation analyses between ISI scores, differential serum biochemical markers, differential metabolites, and key gut microbiota will be performed using Pearson or Spearman correlation coefficients. Missing values for data analyzed using non-mixed effect models will be managed using multiple imputation methods.

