## Discussion

3

This randomized controlled trial aims to evaluate both the clinical efficacy and the potential mechanisms of LSM therapy in treating insomnia among breast cancer survivors. A key feature of this study is the use of a multi-omics approach, which will analyze changes in serum biochemical markers, gut microbiota composition, and metabolomic profiles to provide substantial theoretical support for the therapeutic effects of LSM.

Insomnia is associated with dysregulation across several physiological systems, particularly the nervous, immune, and endocrine systems. This study will focus on key serum biochemical markers, including neurotransmitters (5-HT and GABA), inflammatory cytokines (IL-1β, IL-6, TNF-α), and endocrine hormones (melatonin and hormones related to the HPA axis), as these have been implicated in the pathophysiology of insomnia. Specifically, 5-HT and GABA act as critical inhibitory neurotransmitters that help modulate excessive neuronal activity, and their levels are often reduced in individuals with insomnia (31, 32). Retrospective clinical research has suggested that moxibustion may improve insomnia in coronary heart disease patients by increasing serum levels of 5-HT and GABA (33). Regarding the link between inflammatory cytokines and sleep disturbances, IL-1β, IL-6, and TNF-α are commonly studied markers. A literature review underscores the strong association between elevated levels of these cytokines and the worsening of insomnia symptoms (34). Research has shown that IL-1β and TNF-α may exacerbate sleep disturbances by inhibiting the synthesis and release of neurotransmitters GABA and 5-HT (35). Previous studies have consistently demonstrated that moxibustion may exert anti-inflammatory effects, potentially reducing these cytokines (19, 36).

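### Serum markers and gut microbiota abundance are to be compared by t-test or Mann-Whitney U without baseline adjustment, although every participant gives a baseline sample; this costs precision and leaves the result exposed to chance baseline gaps

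*Protocol article*

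**What the plan says.** Four places in the protocol article bear on this point.

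- **Mechanism outcomes (2.4.3)** sets two sampling times: "Blood and fecal samples will be collected from all participants at baseline and at the end of the treatment period (week 4".
- **Statistical analysis (2.9)** names the method: "For non-repeated continuous variables, such as serum biochemical markers and gut microbiota abundance, between-group comparisons will be performed using either the" t-test or the Mann-Whitney U test, according to distribution. No covariate is named, and the section does not say which value is tested, the week-4 value or the change.
- **The same section** treats the clinical scales and hypnotic dose differently: "a mixed-effects model adjusted for baseline values will be used to compare longitudinal changes from baseline across follow-up time points between groups". That model also has endocrine-therapy status, the randomisation stratum, as a fixed effect.
- **The Discussion (3)** describes the mechanism work as a multi-omics approach, "which will analyze changes in serum biochemical markers, gut microbiota composition, and metabolomic profiles".

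Section 2.9 then carries the serum markers and metabolites that differ between groups, together with key microbiota, into correlation analyses with the ISI.

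**The concern.** A baseline sample is drawn, stored and assayed for every participant, but the named tests have no place for it as a covariate. Two things follow.

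First, precision. Baseline adjustment removes the part of the week-4 variance that the baseline value predicts. A two-group test on week-4 values removes none of it. A two-group test on changes subtracts the whole baseline, which is too much whenever the correlation is below 1.

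Second, chance imbalance. With about 45 to 50 per group, some markers will differ at baseline by chance. Neither version of the test corrects for that in the realised sample.

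The reader also cannot tell which quantity is to be compared, and the two candidates can give different answers on the same data. What is at stake is how well the mechanism outcomes can be read, and the correlation step that builds on markers found to differ.

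**Working it through.** **1. The plan's own figure.** The article gives no power for the mechanism outcomes. Its only calculation, in Sample size (2.8), is for the ISI, and it reproduces.

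- Pilot: "ISI scores decreased by 6.82 ± 4.06 points in the LSM group and 3.24 ± 2.38 points in the WC group from baseline". The difference is 6.82 - 3.24 = 3.58. The pooled SD is sqrt((4.06² + 2.38²)/2) = sqrt(11.074) = 3.328. So d = 3.58/3.328 = 1.076, stated as 1.08.
- Unequal-variance t-test, "with a two-tailed alpha of 0.05 and a power of 0.90, while accounting for a 10% expected dropout rate": power is 0.893 at 19 per group and 0.909 at 20, so 20 per group.
- Dropout: 20/0.9 = 22.2, so 23. Two strata: 2 × 23 = 46, which agrees with "the sample size was adjusted to 46 participants per group". The final size is 50.

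The present point does not touch that calculation. It supplies only the number used below: 50 less 10% = 45 per group.

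**2. Assumptions that the documents do not supply.** The correlation rho between baseline and week-4 values is taken as 0.3, 0.5 and 0.7. The true effect is taken as 0.5 SD of the marker, with equal SDs at both times and two-sided alpha 0.05.

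**3. Relative variance of the three analyses.**

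- t-test on week-4 values: 1
- t-test on changes: 2(1 - rho)
- ANCOVA on baseline: 1 - rho²

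ANCOVA is below week-4 values for any nonzero rho. It is below changes for any rho under 1, because 2(1 - rho) - (1 - rho²) = (1 - rho)². Changes do worse than week-4 values when rho is below 0.5.

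**4. Power.** With relative variance v, the standardised effect is 0.5/sqrt(2v/45), and power is approximately Phi(that value - 1.96). For week-4 values this is 0.5/0.2108 = 2.372, giving 0.66. The difference detectable with 80% power is (1.960 + 0.842) × sqrt(2v/45).

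| rho | Week-4: v, power, detectable | Change: v, power, detectable | ANCOVA: v, power, detectable | Per group for ANCOVA to match 45 on week-4 values |
|---|---|---|---|---|
| 0.3 | 1.00, 0.66, 0.59 SD | 1.40, 0.52, 0.70 SD | 0.91, 0.70, 0.56 SD | 41 |
| 0.5 | 1.00, 0.66, 0.59 SD | 1.00, 0.66, 0.59 SD | 0.75, 0.78, 0.51 SD | 34 |
| 0.7 | 1.00, 0.66, 0.59 SD | 0.60, 0.86, 0.46 SD | 0.51, 0.91, 0.42 SD | 23 |

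The last column is 45(1 - rho²), rounded up. Using the noncentral t distribution instead lowers each power by about 0.01 (for example 0.65 for week-4 values and 0.77 for ANCOVA at rho 0.5).

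**5. Exposure to a baseline gap.** The standard error of a baseline difference is sqrt(2/45) = 0.21 SD. The chance of a gap above 0.3 SD in either direction is 2(1 - Phi(0.3/0.2108)) = 15% for each marker. Given a gap, the expected shift in the estimate is:

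- week-4 values: rho × gap. For 0.3 SD this is 0.09, 0.15 and 0.21 SD at rho 0.3, 0.5 and 0.7.
- changes: (rho - 1) × gap, in the opposite direction: -0.21, -0.15 and -0.09 SD.
- ANCOVA: zero, if the linear model holds.

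For the week-4 t-test, the type I error given a 0.4 SD gap is 0.12 at rho 0.5 and 0.19 at rho 0.7. Given a 0.2 SD gap it is 0.046 and 0.035, slightly under 5%.

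**The case against.** **The split between repeated and non-repeated follows the design.** Each outcome given the mixed model has at least two post-baseline assessments: weeks 2, 4, 6 and 8 for ISI and hypnotic dose, weeks 4 and 8 for the other scales. The samples have one. A model with a time-by-group term does not suit them. This stands. A reader might infer that the plan contradicts itself, but "non-repeated" can well mean measured once after baseline. That does not justify leaving the baseline out, since ANCOVA needs only one post-baseline value.

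**The tests may be meant for changes.** A reader might infer a week-4-only comparison, but section 2.9 does not say so and the Discussion points the other way. If changes are tested, the loss against ANCOVA is modest at high correlation (0.86 against 0.91 at rho 0.7). It is still there (0.66 against 0.78 at rho 0.5), and it grows as rho falls.

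**Randomisation protects the test.** It does, on average. A reader might infer that false mechanism findings become more frequent overall, or that a baseline gap passes in full into the estimated effect. Neither follows. The unadjusted test keeps its 5% error over repeated randomisation; the inflation applies only given a sizeable gap. The shift is rho (or rho - 1) times the gap, not the whole gap.

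**The gain may be small.** At rho 0.3, ANCOVA raises power only from 0.66 to 0.70 over week-4 values. Nothing in the documents tells us rho for these markers.

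**An article leaves detail to the analysis plan.** Which value is tested could be such a detail. The choice of test is not: it is stated, and it excludes covariates.

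**Conclusion.** The point holds as one of efficiency and clarity, and should be fixed. The named tests are valid, but whichever value they are applied to, they are less precise than an analysis adjusted for a baseline that is collected anyway. They also leave each marker's result dependent on the baseline gap that happens to occur.

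The size depends on an unknown correlation. Against week-4 values, ANCOVA gains about 4, 12 and 25 percentage points of power at rho 0.3, 0.5 and 0.7. Against changes, it gains about 18, 12 and 5 points. These figures assume 45 per group, a 0.5 SD effect and roughly normal data on the analysed scale. They do not count any further gain from the endocrine-therapy stratum, for which the documents give no figure.

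The consequence is limited to mechanism outcomes and the correlation analyses built on them. The primary ISI analysis already adjusts for baseline and stratum and is unaffected.

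**What to change.** In section 2.9, replace the t-test or Mann-Whitney sentence, as it applies to serum markers and taxon abundance, with an analysis of covariance. The outcome is the week-4 value, log- or rank-transformed if skewed. The terms are group, baseline value on the same scale and endocrine-therapy status. Report the adjusted difference, or the ratio if analysed on the log scale, with its confidence interval. Replace "non-repeated" with wording such as 'measured once after baseline', and state that both samples are used.

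The same model may be used for short-chain fatty acids and alpha diversity, for which section 2.9 names no test. LEfSe can stay as specified in section 2.4.3.

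The cost is a few lines of text and slightly longer code. The samples are already planned, so no extra visits, assays or participants are needed. The change should be made before group identities are disclosed, so that the choice of model cannot depend on the results.

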Emerging evidence indicates that gut microbiota may influence sleep-wake cycles through immune modulation, hormonal signaling, bacterial metabolites, and neural communication pathways (45). Significant alterations in the diversity, composition, and structure of the gut microbiota have been observed in individuals with insomnia. For instance, a recent Mendelian randomization study identified that the microbial taxa *Enterorhabdus* and *Paraprevotella* were associated with an increased risk of insomnia, whereas *Coprobacter*, *Desulfovibrio*, *Flavonifractor*, *Olsenella*, *Odoribacter*, and *Oscillibacter* were linked to a decreased risk (46). One clinical study reported that insomnia patients, compared to healthy controls, exhibited reduced α-and β-diversity, increased *Bacteroidetes*, and a decreased *Firmicutes*/*Bacteroidetes* ratio (47). Recent studies further suggest that *Bacteroidetes* dominate the gut microbiota of insomnia patients, and good sleep is closely associated with lower *Bacteroidetes* abundance (48). Another study found that the relative abundances of *Lactobacillus*, *Streptococcus*, and *L. crispatus* were significantly higher in insomnia patients compared to non-insomniacs (49). An animal study provided preliminary evidence that moxibustion may restore the normal *Firmicutes*/*Bacteroidetes* ratio and reduce the abundance of *Lactobacillus* and *Proteobacteria*, thereby alleviating chronic fatigue syndrome in rats (50).

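### If LSM lowers a dominant gut phylum, the planned tests on 16S abundances can flag unaffected taxa as raised; how often depends on figures the protocol does not give

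*Protocol article*

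**What the plan says.** Protocol article, 2.4.3 (Mechanism outcomes):
- The assay: "Gut microbiota composition in fecal samples will be analyzed through 16S rRNA gene sequencing".
- The timing: "Blood and fecal samples will be collected from all participants at baseline and at the end of the treatment period (week 4").
- The first method for finding taxa that differ: "The linear discriminant analysis effect size (LEfSe) model will be applied to identify differentially abundant taxa between groups".
- Between-sample diversity: "β diversity will be evaluated through principal coordinates analysis (PCoA) based on the Bray–Curtis distance matrix".

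Protocol article, 2.9 (Statistical analysis):
- The second method: "For non-repeated continuous variables, such as serum biochemical markers and gut microbiota abundance, between-group comparisons will be performed" with a t-test or a Mann-Whitney U test, chosen by the shape of the distribution.
- The later use of the results: "Correlation analyses between ISI scores, differential serum biochemical markers, differential metabolites, and key gut microbiota will be performed" with Pearson or Spearman coefficients.

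Protocol article, 3 (Discussion): Bacteroidetes are said to "dominate the gut microbiota of insomnia patients, and good sleep is closely associated with lower" abundance of that phylum. An animal study is cited in which moxibustion may have restored the Firmicutes/Bacteroidetes ratio.

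The article mentions no log-ratio, compositional model or absolute quantification.

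**The concern.** A serum concentration is an absolute quantity, and one marker can move without moving another. 16S read counts carry only shares that sum to one. When a large group shrinks, the other shares rise even if those bacteria are unchanged. A t-test, a Mann-Whitney test or LEfSe applied to shares registers that rise as a difference between arms.

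The trial's rationale points at this situation: a dominant phylum, lower when sleep is good, with moxibustion expected to shift the balance. The analysis would therefore be least reliable when the hypothesis is true.

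The error has a direction. Unaffected taxa appear raised by LSM, so a false-discovery correction does not remove it. Artefacts could then enter the correlations with ISI, serum markers and metabolites, and so the mechanistic account.

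**Working it through.** **Inputs from the article.** It gives no figure for the microbiota analysis. Only the arm size is taken from it: 50 per group less 10% dropout (2.8), so 50 × 0.90 = 45. The underlying 46 per group reproduces. With a difference of 6.82 − 3.24 = 3.58 and SDs of 4.06 and 2.38, an unequal-variance t-test has power 0.893 at 19 and 0.909 at 20 per group. Then 20/0.90 rounds up to 23, and 23 × 2 strata = 46. The significance level is 0.05 two-sided (2.9).

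**Assumptions, not in the article.** Share *s* of the dominant group is 30-50%, and its remaining fraction *f* is 0.75 or 0.50. The between-person SD of log abundance (log-SD) and the number of taxa vary as stated.

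**Step 1: size of the artefact.** An unaffected taxon's share is multiplied by 1/(1 − s + s·f).

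| s | f | Apparent rise |
|---|---|---|
| 0.30 | 0.75 | 1/0.925 = 1.08 |
| 0.30 | 0.50 | 1/0.850 = 1.18 |
| 0.50 | 0.75 | 1/0.875 = 1.14 |
| 0.50 | 0.50 | 1/0.750 = 1.33 |

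**Step 2: how often an unaffected taxon is flagged.** Simulation with 45 per arm, one dominant feature, 30 unaffected taxa, log-SD 0.8, 20,000 reads and 300 replicates.

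| s, fall | Mann-Whitney on shares | t-test on shares | Mann-Whitney on centred log-ratio |
|---|---|---|---|
| 30%, none | 4.9% | 5.0% | 5.0% |
| 30%, 25% | 7.0% | 6.2% | 5.2% |
| 30%, 50% | 12.8% | 10.5% | 5.0% |
| 50%, none | 4.6% | 4.2% | 4.7% |
| 50%, 25% | 9.5% | 7.8% | 5.2% |
| 50%, 50% | 25.7% | 19.5% | 5.0% |

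Where there is a fall, 86-99.7% of the Mann-Whitney false positives point upward in the LSM arm. LEfSe was not simulated; it also works on relative abundances.

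**Step 3: sensitivity to variance (one dominant feature, Mann-Whitney on shares).**
- Log-SD 0.5-1.0, 60 unaffected taxa: 9-64% when the group is halved, and 6-25% for a 30% fall.
- Log-SD 1.0, falls of 30-50%: 7-16%.
- Log-SD 1.5: about 5-9%.
- Log-SD 2.0: 5-7%.

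The corner with half of reads, halved, at log-SD 0.5 gave 60-64% across separate runs.

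**Step 4: does a plain log-ratio cure it?** Bacteroidetes are a phylum, so a fall would be spread over many features. If *m* taxa halve beside 60 unaffected ones, the centre of the log-ratio itself drops. Unaffected taxa then appear raised by 2^(m/(m+60)): 1.15 for m = 15, 1.26 for m = 30 and 1.32 for m = 40. Simulated error, group halved:

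| Log-SD, s, m | Mann-Whitney on shares | Median-centred log-ratio | Centred log-ratio |
|---|---|---|---|
| 0.5, 30%, 15 | 31% | 23% | 25% |
| 0.5, 30%, 30 | 32% | 52% | 57% |
| 0.5, 50%, 30 | 75% | 53% | 56% |
| 1.0, 30%, 40 | 12% | 25% | 25% |
| 1.0, 50%, 40 | 26-27% | 25% | 25% |

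The order follows the algebra. At s = 30% and m = 30, the log-ratio artefact (1.26) exceeds the closure artefact (1.18); at s = 50%, 1.33 exceeds 1.26. Over a wider set with the fall spread across 15-40 taxa, the plain centred log-ratio gave roughly 7-72%.

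**Step 5: bias-corrected log-ratio.** A test that re-centres on the mode of the taxon-wise differences, an approximation to the ANCOM-BC type of correction, stayed at 5-7% in most settings. It reached about 12% in the noisiest or most diffuse ones. ANCOM-BC itself was not run.

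**Step 6: the phylum ratio.** With total T, log(F/T) − log(B/T) = log F − log B. The total cancels, so closure does not affect the Firmicutes/Bacteroidetes ratio.

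**The case against.** - **The outcome is composition.** The article names gut microbiota composition as its outcome and makes no claim about absolute abundance. As a test of shares, Mann-Whitney is valid, and a risen share is a real compositional difference. This stands: the fault lies in reading a risen share as a taxon raised by LSM, and in choosing key taxa on that basis.
- **The scale is not stated.** Section 2.9 does not say raw proportions, and a t-test on transformed data would fit its wording. This stands in part. A reader might infer that the plan assumes the taxa are independent; it does not say so, and testing one variable at a time does not prove it. But an unseen transformation would have to be a suitable one, and the LEfSe route rests on relative abundance either way. The article also does not define its key taxa as the univariate hits.
- **The size is assumed.** This stands in full. No share, fall, taxon count or variance comes from the article.
- **The obvious remedy can fail.** A reader might infer that any log-ratio restores 5%. That holds when one feature falls. When the fall is spread over a phylum, the plain centred log-ratio can do worse than the plan.
- **Other gaps.** A reader might also count as errors the lack of a rule between LEfSe and the univariate tests, and the lack of a test beside the PCoA. An article commonly leaves such details to the full protocol or analysis plan, so they are not charged here.

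**Conclusion.** The concern holds in a conditional form. The methods named for 16S abundances can report unaffected taxa as raised by LSM if LSM lowers a dominant group, which the article's own Discussion makes plausible. The apparent rise is 1.08 to 1.33 times for an assumed 30-50% share falling by 25-50%.

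The error per unaffected taxon is nominal with no shift. It is roughly 5 to 9.5% for a 25% fall at log-SD 0.8, or for one falling feature at log-SD 1.5 or more. It reaches 60-75% only with half of reads, halved, at log-SD 0.5. Nothing in the article supports treating that upper figure as expected.

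This touches mechanism outcomes only; the primary ISI result is unaffected. It is a worthwhile, cheap improvement, not a defect that threatens the trial.

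**What to change.** Before the sequencing data are analysed, amend 2.4.3 and 2.9 as follows:

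1. Base statements that a taxon differs between arms, and the choice of key taxa for the correlations, on one bias-corrected compositional method, such as ANCOM-BC. Do not rely on a plain centred log-ratio.
2. Keep LEfSe as descriptive. Describe any remaining LEfSe or univariate results as relative, not absolute, changes.
3. Compare the log Firmicutes/Bacteroidetes ratio between arms as a supporting analysis. It need not be the lead microbiota endpoint. It shows that the balance moved, not which phylum moved.
4. Optionally, accompany the PCoA plot with PERMANOVA on the Bray-Curtis distances, permuted within endocrine-therapy stratum.

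The cost is R code, and R is already planned; no new samples are needed. The downsides are less direct comparison with earlier LEfSe reports, and some residual error (up to about 12% in the approximation above) when variance is high or the shift is diffuse.

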## Abstract

**Background:**

Insomnia (difficulty falling or staying asleep) is a common issue among breast cancer survivors, significantly impacting their quality of life. Current treatments, primarily pharmacological and psychological, have limitations: the former often causes side effects, while the latter faces accessibility barriers. Long-snake moxibustion (LSM), a traditional Chinese medicine (TCM) technique, involves applying moxibustion along the governor vessel, which is an important meridian in TCM that plays a key role in regulating brain function. LSM is characterized by its minimal side effects, ease of application, and cost-effectiveness, with preliminary studies supporting its potential for treating insomnia. This study aims to further investigate the therapeutic effectiveness of LSM in alleviating insomnia among breast cancer survivors and to explore its underlying mechanisms.

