#### Safety outcome

2.4.4

All adverse events (AEs) occurring during the study will be comprehensively documented in the clinical research forms (CRFs), detailing the timing, symptoms, severity, interventions, prognosis, and any other relevant information. The severity of AEs will be assessed using the Common Terminology Criteria for Adverse Events (CTCAE) version 5.0 (28), as defined by the National Institutes of Health (NIH), with grades 3–5 classified as severe. The acupuncturist and study team will evaluate the potential causal relationship between the AEs and the LSM treatment. AEs potentially related to LSM may include, but are not limited to, blisters, erythema, pruritus, burns, and respiratory symptoms. Safety monitoring will involve regular assessments of the treatment site, temperature measurements to minimize the risk of burns and excessive erythema. Appropriate interventions will be implemented for all AEs, regardless of their association with LSM. In the event of severe AEs, urgent medical attention will be provided, the study intervention will be discontinued, and the research ethics committee will be notified within 24 h with a detailed report outlining the nature of the event, actions taken, and outcomes. The participant will be closely monitored until the serious AEs are adequately managed. The study team will conduct a thorough review of the severe AEs to determine whether modifications to the study protocol are necessary to prevent recurrence.

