For the primary efficacy outcome (the change in the ISI score from baseline to the end of the 4-week treatment period), subgroup analyses will be conducted based on hypnotic medication use (yes, no) and insomnia severity (mild, moderate, severe) to further explore potential variations in the treatment effects of LSM across different subgroups. Additionally, sensitivity analyses will be performed for the primary efficacy outcome. Specifically, if missing values or non-normally distributed data are present, multiple imputation methods will be used to assess the impact of missing data, and generalized estimating equations will be employed as a non-parametric alternative for non-normally distributed data. Pre-specified per-protocol analyses will also be conducted. The per-protocol set will include all participants who completed the intervention and follow-up according to the study protocol. The results of the primary analysis will be compared with those from these sensitivity analyses to assess robustness.

All statistical analyses will be carried out using SPSS (version 26.0) and R (version 4.3.1). Two-tailed significance testing will be applied, with a *p*-value threshold of ≤ 0.05 indicating statistical significance.

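### Adverse-event incidence is analysed only by a between-arm test, which does not estimate how often moxibustion-specific harms occur under LSM and is insensitive to uncommon ones at 50 per arm

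*Protocol article*

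**What the plan says.** The protocol article, section 2.9 (Statistical analysis), groups adverse events with response rates: "Categorical variables, including treatment response rates and incidence of adverse events, will be analyzed using chi-square or Fisher’s exact tests". The same section closes with a general criterion: "Two-tailed significance testing will be applied, with a *p*-value threshold of ≤ 0.05 indicating statistical significance". It names no other statistical analysis of safety.

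Section 2.4.4 (Safety outcome) lists the harms in view: "AEs potentially related to LSM may include, but are not limited to, blisters, erythema, pruritus, burns, and respiratory symptoms". It also plans individual recording of every event, CTCAE v5.0 grading with grades 3–5 classed as severe, a judgement on relatedness to LSM, checks of the treatment site, and review of severe events. No expected event rates are given.

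The sample size (section 2.8) is built on the ISI alone: "the sample size was adjusted to 46 participants per group", and then "the sample size per group was rounded up to 50 participants".

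The Abstract's background says of LSM: "LSM is characterized by its minimal side effects, ease of application, and cost-effectiveness, with preliminary studies supporting its potential for treating insomnia". The Introduction describes moxibustion in general in similar terms.

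**The concern.** Two features of the stated method fit the safety question badly.

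First, sections 2.1 and 2.3 give LSM only to the LSM arm during the treatment period. A moxibustion burn or blister therefore cannot occur on waitlist, and for these events the null hypothesis of equal incidence is settled by the design. A clinician needs to know how often they happen under LSM and how high the rate could plausibly be. A between-arm p-value supplies neither.

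Second, the trial was sized for a large effect on a continuous score. With 50 per arm, a test on a binary event is insensitive to harms of around 10% or less, and to modest excesses over a non-zero background rate. A non-significant result in that range carries little information about harm.

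At stake is how informative the safety report will be. The planned data can support a useful upper limit on risk, but the stated analysis does not ask for one.

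**Working it through.** **Inputs from the article.** 50 per arm, 1:1 allocation, two-tailed p ≤ 0.05, chi-square or Fisher's exact test, 10% expected dropout (50 × 0.9 = 45 per arm).

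**Assumptions, because the article gives no event rates.** True LSM risk of 5% to 20% for a site event; zero waitlist events for moxibustion-specific harms; for overall adverse events, background rates of 5% or 10%.

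**The plan's own figure.** The pilot ISI changes (6.82 ± 4.06 and 3.24 ± 2.38, difference 3.58) in an unequal-variance t-test at two-sided 0.05 give power 0.893 at n = 19 and 0.909 at n = 20. Dropout: 20 / 0.9 = 22.2, so 23. Two strata: 2 × 23 = 46 per group, as stated. The size follows from the ISI; safety plays no part in it.

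**Step 1. Where Fisher's test becomes significant.** For k/n against 0/n with equal arms, the two-sided p is 2 × C(n, k) / C(2n, k). At n = 50:
- k = 4: p = 0.117
- k = 5: 2 × 2,118,760 / 75,287,520 = 0.056
- k = 6: 2 × 15,890,700 / 1,192,052,400 = 0.027

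So six LSM events (12%) are needed; five (10%) are non-significant. At n = 45 the threshold is also six (k = 5: 0.056; k = 6: 0.026).

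**Step 2. Probability of missing a harm.** Miss rate = P(X ≤ 5), X ~ Binomial(n, p):

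| True LSM risk (assumed) | n = 50 | n = 45 |
|---|---|---|
| 5% | 96% | 98% |
| 10% | 62% | 71% |
| 15% | 22% | 31% |
| 20% | 5% | 9% |

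**Step 3. Chi-square in place of Fisher.** Uncorrected chi-square is significant from k = 4 (p = 0.041), with power of 24% at a risk of 5% and 75% at 10%, against 4% and 38% for Fisher. With four events in total the expected event count is 2 per arm, which conventionally points to Fisher.

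**Step 4. Overall adverse events.** Fisher power at 50 per arm, by enumerating all tables: 24% for 5% against 15%, 20% for 10% against 20%, 41% for 10% against 25%.

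**Step 5. What an estimate would give.** Exact (Clopper-Pearson) two-sided 95% limits for n = 50:
- 0/50: upper limit 1 − 0.025^(1/50) = 7.1%
- 2/50: 0.5% to 13.7%
- 5/50: 3.3% to 21.8%

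The 5/50 result, which the test labels non-significant, is reported here as a risk that could exceed one in five.

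**The case against.** The strongest reply is that the article makes no mistake of inference. It states no safety hypothesis, margin or decision rule tied to the test, and nowhere says that p > 0.05 means safe. That stands. A reader might infer that a non-significant test is meant to confirm the low side-effect burden, but that description appears only as background in the Abstract and Introduction. It is neither an endpoint nor a planned conclusion.

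A reader might also infer that the test is the only safety evidence planned. It is not: section 2.4.4 provides recording, grading, relatedness and treatment-site checks, so rare harms can be described whatever the p-value. It is the only statistical analysis of safety stated, which is a narrower claim.

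Third, one might say that the test misses most relevant harms. The article gives no rates, so this cannot be established. For common local effects it is false: at 20% against 0%, Fisher detects about 95%.

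Fourth, section 2.9 speaks of incidence in general and does not commit to event-by-event tests. Erythema, pruritus and respiratory symptoms can occur on waitlist, so the zero comparator applies only to moxibustion-specific events. That also stands and limits the scope.

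Finally, adverse-event tables and intervals are often left to a fuller document, and their absence alone would be no finding. The point here rests on the method that the article does name and on what that method cannot show. Low power for uncommon harms is common to any trial of 100 patients; it argues for estimation as the main safety analysis.

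**Conclusion.** The point holds as a modest improvement to a stated method. It does not correct an error in any stated conclusion. For moxibustion-specific events the between-arm test leaves the frequency under LSM unaddressed. For uncommon harms it is insensitive: with 50 per arm and no waitlist events, Fisher's test misses 96% at a true risk of 5%, 62% at 10% and 22% at 15%, falling to about 5% at 20%. These figures rest on assumed event rates, all 50 per arm evaluable, and Fisher as the test applied. Uncorrected chi-square would be more sensitive, and 45 per arm would be less so.

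**What to change.** In section 2.9, make the main safety analysis:

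- (a) for each treatment-site event, the proportion of LSM participants affected, with an exact (Clopper-Pearson) 95% confidence interval;
- (b) for overall and grade 3–5 adverse events, the between-arm risk difference with its 95% confidence interval.

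Keep any between-arm chi-square or Fisher test as descriptive only; deleting it is optional. Add that a non-significant p-value will not be taken as evidence of safety.

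The cost is a wording change and a few lines of code, with no extra patients, visits or data. The downside is a less favourable safety statement: even with no site events among 50, the trial could exclude only risks above about 7%.
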